### Randomization {16a} {16b} {16c}

Randomization will be carried out using a simple randomization based on an equiprobable algorithm. According to randomization algorithm, a three-digit numerical code list will be generated with the R statistical software. It contains the three-digit and the assignation group. This list will be given to the laboratory and to the pharmacy service of the DUH, so only these both will know which of the groups is placebo and which of the groups is experimental. Only the part of the lists containing the 70 three-digit numerical code (not the assignation group) will be given to the main investigator. For each recruited patient, the main investigator will assign consecutively a three-digit code number and give to the patient a document with his name and the three-digit numerical code. When the patient will go to the laboratory, it will know if the patient belongs to the experimental group or the placebo group and proceed to prepare the samples. The principal investigator and the patients will be blinded for the remaining.

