### Data collection {18a} {18b} {19} {27}

At baseline, patient demographics and prior failed therapies will be documented, including frequency, duration, type, and compliance, as well as magnetic resonance imagining (MRI) and electromyography (EMG) diagnostic tests. Documentation of analgesic use for the treatment of LLR will include frequency, dosage, and duration. All baseline and post-procedural follow-up points will include reported outcomes documented through completing the NPRS, ODS, MOAS, SF-12, and DN4 questionnaires and documentation of narcotic and non-narcotic analgesic medication usage. Device and procedure-related adverse events and all serious adverse events will be documented throughout the study period (Table 3).

The data collected will be stored in locked cabinets, and only the main researcher will have access to this information. Data will be recruited in a computer spreadsheet with password protection to ensure confidentiality. To ensure no error, the spreadsheet will be monthly monitored and audited by a researcher who is blind to the participants’ group allocation and has no conflict of interest.

All patients who leave the study for any reason will no longer have their data collected.

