### Monitoring, safety, and quality control

The primary safety endpoint is the incidence of device- and/or procedure-related adverse events, which will be compared statistically between the randomized groups using proportions of patients experiencing such an event. The endpoint will be met if this event rate is not significantly greater with ACS than with PhS. All study-related adverse events will be monitored and reported, including seriousness, severity, treatment, and relationship to the study device/procedure. Adverse events collected in this study will be determined by the mine investigator to be specifically related to the products or procedures used in the 2 treatment groups or one that is determined to be a serious adverse event {22}.

To date, all published studies with ACS have shown high safety rates and no side effects for what ACS product itself represents. Even so, any intervention can lead to an adverse effect, so their monitoring will be an essential condition in this protocol {11b}.

Once the study has started, given that the inclusion of patients will be progressive over time as they are recruited, just in case there is a worsening of pain of more than 25% in more than 50% of the patients, the study would be reconsidered and the recruitment would be stopped to analyze the data and check if the worsening is in patients whom the ACS therapy was applied. If this were the case, the study would be definitively stopped and a report would be given to the laboratory. The author responsible for the study will carry out this audit if necessary. The main investigator together with the rest of the authors will make the decision to terminate the trial early {17b} {21a}.

Any other adverse effect as far as the interventions are concerned will be collected and analyzed (if necessary, the second intervention would be canceled, and the patient would be withdrawn from the study) {11b} {21b}.

The main investigator is the only person who will be in charge of follow-up with clinical interviews at 30 days, 3 months, 6 months, and 12 months. A schedule of visits will be established for each patient for their greater adherence to the study and not to delay follow-up. Apart from the following-up visit controls, the patients will provide from a telephone number of pain unit for any doubts, changing pain characteristics, or new interventions they will receive. In that way, it provides an improving of adherence to protocol of the study {11c}.

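### Non-serious adverse events are recorded only if the main investigator first judges them related, so misattributed events are lost for good and the arms cannot be compared free of attribution

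*Protocol article*

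**What the plan says.** Two sections of the protocol article set the scope of adverse event recording, and they agree.

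- *Monitoring, safety, and quality control*: "Adverse events collected in this study will be determined by the mine investigator to be specifically related to the products or procedures" used in the two arms, "or one that is determined to be a serious adverse event".
- *Data collection*: "Device and procedure-related adverse events and all serious adverse events will be documented throughout the study period".

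A further sentence in the monitoring section reads "Any other adverse effect as far as the interventions are concerned will be collected and analyzed". It is tied to the interventions, so it does not clearly widen the scope to events thought unrelated.

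The endpoint is defined in the same section: "The primary safety endpoint is the incidence of device- and/or procedure-related adverse events", compared between arms as proportions of patients. The success rule is "The endpoint will be met if this event rate is not significantly greater with ACS than with PhS". No margin, expected event rate or named test goes with it.

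On who decides, the monitoring section makes the main investigator the only person responsible for the follow-up interviews at 30 days and 3, 6 and 12 months. The *Randomization* section states: "The principal investigator and the patients will be blinded for the remaining".

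**The concern.** Relatedness is normally an attribute attached to an event already on record. Here it is the condition for recording. Three things follow for non-serious events.

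1. If a truly related event is judged unrelated, no trace remains. The monthly spreadsheet audit under *Data collection* can check entries, not events that were never entered.
2. Nobody can reassess the judgement later, whether blinded or after unblinding. The monitoring section promises to report each event's relationship to the device or procedure, but that has little content for non-serious events if only related ones are kept.
3. The arms cannot be compared on a measure that needs no causal judgement. Randomisation and blinding make exactly that comparison possible, and it matters most for an unexpected effect that nobody thinks to attribute to the serum.

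The success rule gives the direction of the first consequence: because non-significance counts as success, any loss of true events makes success more likely. This cannot be left to an analysis plan, since no analysis recovers events that were not recorded.

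**Working it through.** **Inputs.** From the documents: 35 patients per arm (*Sample size*) and a 5% significance level (*Statistical analysis*). The plan gives no safety event rate, margin or power, so there is no safety figure of its own to reproduce. Assumed here: true proportions of patients with a related event of 30% (ACS) and 10% (saline), with 20% and 10% as a second case; a capture share s, equal in both arms because the assessor is blinded; and a two-sided test at 5%, either chi-square without continuity correction or Fisher.

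**Step 1: does dropping truly unrelated events change the endpoint?** No. The endpoint counts patients with a device- or procedure-related event. An unrelated non-serious event would not count even if recorded.

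**Step 2: what if some truly related events are judged unrelated?** The recorded proportions become 0.30s and 0.10s, and the difference 0.20s. Equal loss in both arms still weakens the comparison. Using z = difference / √(2·p̄(1−p̄)/35), with p̄ the mean of the two proportions:

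- s = 1: 0.20 / √(2 × 0.20 × 0.80 / 35) = 0.20 / 0.0956 = 2.09
- s = 0.5: 0.10 / √(2 × 0.10 × 0.90 / 35) = 0.10 / 0.0717 = 1.39

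Exact probability that the endpoint is met = 1 − Σ P(a)P(b) over all pairs (a, b) in which ACS is significantly greater, with a ~ Bin(35, 0.30s) and b ~ Bin(35, 0.10s):

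| Capture s | Recorded rates | Chi-square | Fisher |
|---|---|---|---|
| 100% | 30% vs 10% | 44% | 54% |
| 90% | 27% vs 9% | 49% | 60% |
| 75% | 22.5% vs 7.5% | 56% | 70% |
| 50% | 15% vs 5% | 69% | 86% |

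For true rates of 20% vs 10%, the figures are 78% (chi-square) and 87% (Fisher) with full capture, and 88% and 97% at 50% capture.

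**Step 3: would comparing all events instead be more sensitive?** Add an independent background event rate u, equal in both arms. The any-event proportion is 1 − (1 − p)(1 − u). With p = 30% vs 10%:

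| Background u | Any-event rates | Chi-square | Fisher |
|---|---|---|---|
| 10% | 37% vs 19% | 61% | 70% |
| 20% | 44% vs 28% | 71% | 78% |
| 40% | 58% vs 46% | 85% | 89% |

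These are again probabilities of finding no significant excess. All exceed the 44%/54% for fully captured related events, so an any-event comparison is less sensitive than a well-measured related-event one.

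**The case against.** A reader might infer that the filter itself biases the primary safety endpoint towards success. The documents do not support that. Collection and endpoint have the same scope, so discarding truly unrelated events takes nothing from the endpoint and spares it noise (steps 1 and 3). The assessor is blinded, so the text gives no ground for a filter that differs by arm. Easing arises only through misjudged related events, and the documents give no way to estimate that share. At 90% capture the shift is only about 5 to 6 percentage points.

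A reader might also take the statement that "all published studies with ACS have shown high safety rates and no side effects" as evidence that the investigator will lean towards calling events unrelated. The statement concerns the ACS product, and the next sentence accepts that any intervention can cause harm and calls monitoring essential. It shows no such leaning.

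Nor would harm go wholly unseen. Serious events are kept whatever their cause. Pain, DN4, function and analgesic use are recorded at each follow-up point for patients still in the study, and worsening pain has its own check.

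Finally, most of the easy pass comes from treating non-significance as success with 35 per arm: a true tripling passes in 44% to 54% of trials even with full capture. Recording more events does not change that rule, and the same blinded person would still assign relatedness.

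All of this stands, and it limits the point. It does not answer the permanent loss of misjudged non-serious events, the inability to recheck those judgements, or the absence of any attribution-free comparison.

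**Conclusion.** The concern holds in limited form. The plan makes one blinded person's relatedness judgement the condition for recording a non-serious event, and whatever that judgement gets wrong cannot be recovered. The related-event endpoint is not biased by the filter as such. It becomes easier to meet only to the extent that truly related events are misjudged, and that extent is unknown.

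Under the assumed 30% vs 10%, misjudging 10% to 50% of related events equally in both arms raises the chance of meeting the endpoint from 44% to between 49% and 69% (chi-square), or from 54% to between 60% and 86% (Fisher). These are illustrations: the event rates and capture shares are assumptions, and the safety test is not named. The firm findings are the lost record and the lost comparison. The change is worth making because it is cheap and the loss is irreversible.

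**What to change.** Cheap improvement. Amend *Data collection* and *Monitoring, safety, and quality control* so that every adverse event is recorded at the existing follow-up visits and calls. Relatedness is then assigned while blinded, as an attribute of the recorded event and not as a condition for recording it.

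Keep the proportion of patients with a related event as the primary safety endpoint. Report the proportion with any adverse event by arm beside it, not in its place. Give each a 95% confidence interval for the difference between arms.

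Cost: slightly more recording per contact and one extra table, with no added visits or procedures. The any-event comparison is less sensitive because background events dilute it, which is why it should accompany the related-event endpoint and not replace it.

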### Outcome measures and follow-up {12}

#### Primary outcome

The primary outcome will be level pain using Numeric Pain Rating Scale (NPRS). The NPRS is a segmented numeric version of the visual analog scale (VAS) in which a respondent selects a whole number (0–10 integers) that best reflects the intensity of his/her pain. A reduction of ≥ 2 points in NPRS is considered clinically significant pain relief [40]. This outcome will be measured at baseline at the moment of clinical interview and decision to recruitment and CI singed. This outcome will be measured again after the second intervention at 30 days, 3 months, 6 months, and 12 months after the intervention.

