### Statistical analysis {20a} {20b} {20c} {18b}

A descriptive analysis will be carried out for all the data collected. The normality of the data will be studied using the Kolmogorov–Smirnov and Shapiro–Wilk tests. For continuous quantitative variables, descriptions of central tendency and dispersion will be presented: mean and standard deviation respectively in case the variables follow a normal distribution or median and interquartile range for those variables that are not normally distributed. For categorical (qualitative) variables, frequencies and percentages will be presented. The main outcome (improvement > 2 points) will be tested using a generalized linear mixed model (GLMM). The GLMM model fit will include a between-subject factor and will also include a random effect for the time (baseline, 1st month, 3th month, 6th month, and 12th month) and the interaction between group and time variables. The inclusion of the interaction terms allows for a formal test between the groups over time. For the other variables, the mean effects of the interventions and the differences between groups and their respective 95% confidence intervals will be calculated using regression linear mixed models for repeated measures, which will incorporate terms for the treatment groups, time, and interaction terms. Treatment coefficients versus time interactions will be equivalent to the estimates of the differences between groups. All models will be adjusted for chance imbalances in outcome between groups at baseline. There will also be analyses of the covariates collected, including age, gender, and duration of symptoms. The analyses will follow the principles of intention to treat, and no interim analyses will be performed. No additional analysis will be performed. If a patient drops out of treatment, no additional outcome will be collected. The significance level will be set at 5%, and SPSS for Windows will be used for the statistical analysis.

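### The stopping rule for worsening pain is meant to catch harm from ACS, but its trigger is a rate pooled over both arms, so it is insensitive to harm confined to ACS

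*Protocol article*

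**What the plan says.** The rule is in the protocol article, section Monitoring, safety, and quality control. Recruitment stops and the data are analysed "just in case there is a worsening of pain of more than 25% in more than 50% of the patients". The purpose of that analysis is to "check if the worsening is in patients whom the ACS therapy was applied". If so, the trial ends for good and the laboratory is told. The section notes that patients enter progressively, but gives no reading schedule and no minimum number of patients.

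Four other statements bear on it:

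- Randomization: "Randomization will be carried out using a simple randomization based on an equiprobable algorithm". The abstract gives the ratio as 1:1, with 35 per group.
- Randomization: "This list will be given to the laboratory and to the pharmacy service of the DUH", and no one else knows the allocation. "The principal investigator and the patients will be blinded for the remaining".
- Data collection: the data are kept so that "only the main researcher will have access to this information".
- Statistical analysis: "no interim analyses will be performed".

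**The concern.** A definitive stop depends on the worsening being in ACS patients, so harm from ACS is what the rule is there to find. Yet the first stage counts all patients. It cannot be read as an ACS-arm rate: it names no arm, the investigator who runs it is blinded, and the second stage would be redundant if the first were already by arm.

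Placebo patients who do well therefore dilute the signal. The more specific the harm is to ACS, the less likely the rule is to fire, which is the reverse of what is wanted. This is the only stated provision under which worsening pain halts recruitment and leads to a look by arm. If most ACS patients worsened and few placebo patients did, patients could go on being randomized to ACS.

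**Working it through.** The protocol states no operating characteristics for this rule, so there is no figure of its own to reproduce.

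**Inputs from the protocol.** 70 patients, 35 per arm; 1:1 simple randomization; trigger at strictly more than 50% of patients.

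**Assumed inputs.** The true worsening rates pA (ACS) and pP (placebo) and the reading times. A range is shown for each.

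**Step 1, expected rate.** At 1:1 the pooled rate is (pA + pP)/2, which exceeds 0.5 only if pA + pP > 1. With pP = 10%, pA must exceed 90%; with pP = 30%, it must exceed 70%. At 35 + 35 with pA = 100% and pP = 0, the rate is 35/70 = 50.0%, which is not more than 50%. Likewise 24/35 worsening on ACS against 4/35 on placebo (Fisher p about 2 × 10⁻⁶) is 28/70 = 40%, so no trigger.

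**Step 2, one reading at 70 patients.**
- Pooled, exactly 35 + 35: P(X_A + X_P ≥ 36), the sum of two binomials.
- Pooled, simple randomization: P(Bin(70, (pA + pP)/2) ≥ 36).
- ACS arm only: P(Bin(35, pA) ≥ 18).

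| pA / pP | Pooled, 35 + 35 | Pooled, simple randomization | ACS arm |
|---|---|---|---|
| 80% / 10% | 0.086 | 0.168 | >0.999 |
| 70% / 10% | 0.010 | 0.035 | 0.994 |
| 60% / 10% | 0.0006 | 0.0035 | 0.886 |

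**Step 3, repeated readings.** Simulated trials with fair-coin allocation and no outcome delay. The ACS-arm rule needs at least 10 ACS patients. The last column reads the pooled rule at every patient from the tenth.

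| pA / pP | Pooled at 20/40/60 | ACS arm at 20/40/60 | Pooled, every patient |
|---|---|---|---|
| 80% / 10% | 0.36 | 1.00 | 0.62 |
| 70% / 10% | 0.17 | 0.99 | 0.40 |
| 60% / 10% | 0.06 | 0.90 | 0.23 |
| 70% / 20% | 0.36 | 0.99 | 0.62 |
| 70% / 30% | 0.62 | 0.99 | 0.82 |
| 70% / 40% | 0.84 | 0.99 | 0.94 |

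**Step 4, is the gain only a looser rule?** Read both rules at every patient, the pooled one from the tenth patient and the ACS-arm one from the tenth ACS patient. With equal worsening in both arms, false pauses are nearly the same: 0.014 and 0.015 at 20%, 0.11 and 0.11 at 30%, 0.40 and 0.38 at 40%. Detection is not: 0.40 against 0.998 at 70%/10%, and 0.23 against 0.95 at 60%/10%. The loss comes from the pooled denominator, not from a stricter false-alarm rate.

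**The case against.** The strongest reply is that the worst figures do not describe the rule in use. The 100%/0% case fails to fire only with exactly 35 per arm and one final reading. Under simple randomization it fires with probability 0.45 at one reading of 70, 0.62 at 20/40/60, and 0.82 if read at every patient from the tenth. A reading at 70 has no recruitment left to stop. Even-numbered readings also penalise a strict majority rule, because ties do not fire: at 15/35/55 the pooled rule gives 0.47, 0.27 and 0.13 for 80%, 70% and 60% on ACS against 10% on placebo. Frequent reading is plausible, given the monthly spreadsheet audit and monthly supervision meetings, though neither is said to apply this rule. All of this stands, and it is why the repeated-reading figures carry the conclusion. It does not close the gap: reading every third patient from the ninth still gives only about 0.40 at 70%/10%, while the ACS-arm rule read at 15/35/55 gives 0.99.

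Low placebo worsening is also an assumption, since both arms receive pulsed radiofrequency and an injection. That stands too; where placebo patients worsen often, the pooled rule works tolerably.

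Pooling first protects the blind. But the pharmacy already knows the allocation and, by the same monitoring section, has committed to help control and monitor the trial, so the arms can be counted without unblinding the investigator.

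Adverse event reporting, cancellation of the second injection, follow-up visits and the telephone line all soften the consequence. None is stated to prompt a look by arm during recruitment.

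**Conclusion.** The concern holds. The rule is not useless: frequent reading helps, and so does worsening on placebo. It is weak in the case it was written for. With 10% worsening on placebo and 60% to 80% on ACS, it fires with probability 0.06 to 0.36 at three readings and 0.23 to 0.62 if read at every patient from the tenth. The same threshold on the ACS arm gives 0.90 to 1.00 at the three readings.

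The condition that the two rates must sum to more than 100% needs no outside figure. The probabilities rest on assumed worsening rates, assumed reading times and immediate outcomes. This should be fixed: it concerns participant safety, the other safeguards are partial, and the repair is cheap.

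**What to change.** Keep the sponsor's criterion (worsening of more than 25% in more than 50%) but apply it to the ACS arm.

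- The hospital pharmacy tabulates it at fixed intervals, for example at 20, 40 and 60 enrolled, once about 10 ACS patients have been assessed.
- The main investigator sends only the three-digit code and worsened yes/no, and receives only stop or continue.
- A stop signal pauses recruitment. Before a definitive stop, the ACS rate is compared with the placebo rate against an excess the sponsor sets in advance. This replaces the present second-stage check, which no longer filters anything once an ACS-arm trigger has fired.
- Amend the data-access wording under Data collection, and note under Statistical analysis that this is a safety tabulation with no efficacy test.

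**Cost.** Beyond the tabulation and wording, there are more false pauses than with a pooled rule at the same readings. At 20/40/60, ACS arm against pooled, with equal worsening in both arms: 0.005 against 0.0005 (20%), 0.05 against 0.02 (30%), 0.24 against 0.17 (40%). The second step trims these. If a definitive stop also needs an excess above 25 percentage points (an illustration) and recruitment otherwise resumes, false stops are 0.004, 0.03 and 0.08, detection at 70%/10% stays 0.99, and at 70%/40% it falls to 0.775. A stop signal also tells the investigator that ACS patients had worsened.

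**Two limits remain.** First, outcomes lag: the first post-treatment score comes 30 days after the second injection, itself 14 days after the first. At 70/24, about 3 patients a month, some 4 to 5 enrolled patients are unassessed at any time. With 15 assessed at the first look, the chance of having 10 ACS patients is about 0.15 (0.59 without delay), so the first usable look is often the second. Second, if pain here means the primary outcome scale, on which "a respondent selects a whole number (0–10 integers) that best reflects the intensity of his/her pain", then 10/8 = 1.25, so a patient starting at 8 or more cannot worsen by more than 25%. The fix inherits this from the criterion.

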### Sample size {14}

Based on the existing bibliography in relation to the treatment of pain by ACS treatment for other similar affections [32], it is estimated that accepting an alpha risk of 0.05 and a beta risk of 0.2 in a bilateral contrast, 35 subjects in the treatment group and 35 in the placebo group are needed to detect as statistically significant the difference between the proportion of patients with reduction pain of two points on the NPRS scale, which for the intervention group is expected to be 65%, and for the control group, it is expected to be 35%. A rate of loss to follow-up of 10% has been estimated.

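### Pain worsening of more than 25%, the plan's own trial-ending harm, is compared by arm only after a pooled trigger that responds poorly to an ACS excess; it should be reported by arm at the end regardless

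*Protocol article*

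**What the plan says.** All of the safety text is in the protocol article under Monitoring, safety, and quality control.

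- **Stopping rule.** It is set off "just in case there is a worsening of pain of more than 25% in more than 50% of the patients". No arm is named, so the proportion is taken over both arms. Only then "recruitment would be stopped to analyze the data and check if the worsening is in patients whom the ACS therapy was applied". If the worsening is in ACS patients, the trial ends. No look times and no minimum number of patients are given.
- **Safety endpoint.** The proportions of patients with device- or procedure-related adverse events are compared between arms. "The endpoint will be met if this event rate is not significantly greater with ACS than with PhS". On what counts: "Adverse events collected in this study will be determined by the mine investigator to be specifically related to the products or procedures", or else the event must be serious.
- **Other adverse effects.** "Any other adverse effect as far as the interventions are concerned will be collected and analyzed". The word *other* suggests that worsening is itself seen as an adverse effect, but no between-arm comparison of it is named.

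Elsewhere:

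- **Primary outcome.** Pain is scored on the NPRS, where "a respondent selects a whole number (0–10 integers) that best reflects the intensity of his/her pain".
- **Statistical analysis.** The NPRS is tested as a responder outcome (improved by the threshold or not) in a generalized linear mixed model. Linear mixed models are for the remaining variables. Descriptive statistics are promised for all data: centre and spread for quantitative variables, frequencies and percentages for categorical ones. The section also says that no additional analysis will be done.
- **Randomization.** "Randomization will be carried out using a simple randomization based on an equiprobable algorithm", so arm sizes can differ by chance.

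**The concern.** The plan singles out one harm as serious enough to end the trial, then makes the by-arm view of it depend on a pooled proportion. A pooled proportion reflects the average of the two arms and not the gap between them. A treatment could double or triple the rate of worsening without moving the average past one half.

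The final analysis does not clearly make up for this. The responder outcome puts a patient who worsened by four points in the same class as one who did not change. The safety endpoint counts worsening only if it is judged related or serious, and worsening of a chronic pain condition can easily be put down to the condition. Means or medians of the NPRS do not show what share of each arm worsened.

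So the safety endpoint could be declared met without the plan's own stopping harm having been compared between arms. A positive primary result would not settle the matter, as the last step of the working shows.

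**Working it through.** **Inputs.** From the documents: 35 per arm, 70 in total, 10% loss, two-sided 5% level (Sample size); simple 1:1 randomization (Randomization); trigger at more than 50% of patients pooled (Monitoring). Assumed, because the documents give no figures: the worsening rates and the look times. The plan states no operating characteristic for the trigger, so there is no figure of its own to reproduce.

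**Step 1: what the trigger responds to.** With equal arms the expected pooled rate is (rate on ACS + rate on saline)/2. It passes 50% only if the two rates sum to more than 100%. With exactly 35 per arm, 100% against 0% gives 35/70 = 50%, which is not more than 50%. Under simple randomization arm sizes vary, and the same extreme case meets the trigger in about 45% of trials at N = 70.

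**Step 2: chance that the trigger fires.** Single look: P(X_ACS + X_PhS ≥ 36), with X_ACS ~ Bin(35, p_ACS) and X_PhS ~ Bin(35, p_PhS), by exact convolution. Repeated looks: under simple randomization each patient worsens with probability (p_ACS + p_PhS)/2, and an exact recursion gives the chance that the running count ever exceeds half of those enrolled, checking after every patient from a given start up to 70.

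| ACS vs PhS (assumed) | Single look 35+35 | From patient 20 | From 10 | From 5 | From 1 |
|---|---|---|---|---|---|
| 30% vs 10% | 1e-9 | 0.1% | 1.5% | 7% | 25% |
| 50% vs 10% | 2e-5 | 4% | 11% | 23% | 43% |
| 60% vs 10% | 0.06% | 12% | 23% | 36% | 54% |
| 60% vs 20% | 2% | 28% | 40% | 52% | 66% |
| 80% vs 10% | 9% | 52% | 62% | 70% | 79% |
| 90% vs 10% | 42% | 77% | 82% | 86% | 90% |

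The recursion takes each patient's outcome as known at the look and gives each patient one outcome. Counting worsening at any of the four follow-up visits would mean higher rates, that is, a lower row of the table.

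**Step 3: is early firing sensitivity or noise?** Under simple randomization the chance depends only on the mean rate. (50+10)/2 = (40+20)/2 = (30+30)/2 = 30%, so 50% vs 10%, 40% vs 20% and no difference at all (30% vs 30%) share one row: 4%, 11%, 23%, 43%. The rise with earlier looks comes from small denominators and not from the ACS excess.

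**Step 4: what a by-arm comparison at the end could show.** Exact power of a two-sided 5% Fisher test at 35 per arm, and at 31 per arm (35 × 0.9 = 31.5, rounded down), with the Wald 95% half-width 1.96·√{[p₁(1−p₁) + p₂(1−p₂)]/n}:

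| ACS vs PhS | Power, 35 / 31 | 95% half-width, 35 / 31 |
|---|---|---|
| 20% vs 10% | not computed | 0.166 / 0.176 |
| 30% vs 10% | 0.46 / 0.39 | 0.181 / 0.193 |
| 50% vs 10% | 0.95 / 0.93 | 0.193 / 0.205 |
| 50% vs 20% | 0.69 / 0.62 | 0.212 / 0.225 |

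**Step 5: does the responder analysis stand in for it?** Take 35% responders in both arms and worsening of 50% vs 10%. A Fisher test of responders at one visit, 35 per arm, is significant in 3% of trials. In the other direction, the design assumption for responders, "which for the intervention group is expected to be 65%, and for the control group, it is expected to be 35" percent, is compatible with 30% vs 10% worsened: 65 + 30 = 95 and 35 + 10 = 45, with the remaining 5% and 55% in between.

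**The case against.** **This is a table that an article leaves to the SAP.** That holds for the layout of safety tables. The point here is something the article does fix: a by-arm look at this harm conditional on a pooled trigger. An unconditional look is a better rule.

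**The statement that no additional analysis will be done bars the comparison.** A reader might infer this, but the text does not support it. The Statistical analysis section does not list the adverse-event comparison promised under Monitoring either, so it is not a closed list for safety. One clarifying sentence is enough.

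**Worsening is partly covered already.** This stands in part. Worsening judged related enters the by-arm adverse-event comparison, and disability, mood, quality of life and DN4 are compared by arm with confidence intervals; a large ACS excess could well show there. It would be wrong to say that harm is never compared between arms. What is missing is a comparison of the named harm itself.

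**The pooled trigger protects blinding and is only a backstop.** This is fair: the investigator is blinded, and the rule claims no operating characteristics. It is a reason not to look by arm during recruitment, but no reason to omit the comparison at the end.

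**The trigger fires more often with early looks, and the scenarios are hypothetical.** Both are true, which is why the full range of looks is shown. The gain from early looks would appear equally with no difference between arms.

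**The trigger figures do not support a fix that leaves the trigger alone.** Correct as far as it goes. They show only that the trigger cannot be relied on to bring about the by-arm comparison. The value of the table rests on step 4.

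**Conclusion.** The point holds as a worthwhile and cheap improvement. The trigger is a poor route to a by-arm look: at an assumed 50% vs 10% it fires with probability 2e-5 at a single look, and in 4% to 43% of trials with continuous looks depending on where they start, much of that noise. It becomes likely under late or single looks only for extreme excesses. No other named analysis compares worsening of more than 25% by arm, and the NPRS responder outcome merges worsened with unchanged patients.

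Two stronger readings are not supported. One is that the trigger can never fire: the 100% vs 0% case holds only for exactly equal arms. The other is that ACS is likely to worsen pain: the documents give no worsening rate and report a good safety record for ACS.

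The size rests on assumed rates and look times and on one outcome per patient. A by-arm comparison would detect a large excess (power 0.95 / 0.93 at 50% vs 10%) but often not a moderate one (0.46 / 0.39 at 30% vs 10%).

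**What to change.** At the final analysis, whether or not the trigger was met:

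1. Report by arm and visit the number and proportion of patients whose NPRS worsened by more than 25% from baseline, with the between-arm difference and 95% CI, as a descriptive safety result.
2. Add an increase of at least 2 points as a supplement. The article does not say what the 25% is relative to. If it is baseline NPRS, a patient starting at 8 or 9 would need 3 more points, above the maximum of 10, and one starting at 10 cannot worsen, so patients at 8 or more could never count.
3. State that the sentence on additional analyses does not exclude this table.
4. Do not base the safety conclusion on the related-event comparison alone.

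**Cost.** One table from NPRS data already collected at every visit; no new data and no change in sample size. The downside is one more descriptive comparison, with a 95% CI of about plus or minus 17 to 23 points at 31 to 35 per arm, so moderate excesses would often stay inconclusive. The table improves the final safety conclusion only. It does not make the stopping trigger protective during recruitment.
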